## Methods and Design

### Overview

Patients in a primary-care setting who have had low adherence to AHT, as assessed by the Morisky-Green or Haynes-Sackett tests, and elevated BP will be inform and ask to sign informed consent, those patients that agree to participate will be randomized equally to a "multifactorial intervention" group or a control group (which continued the usual care) (Figure 1). Participants in the intervention arm will receive three intervention sessions during a 9-month period. The intervention will be provided by study nurses who will have received special training for administration of motivational interviewing and in the implementation of the study protocol.

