**Figure 1 F1:**
[figure not shown]
**Study design Flow-chart**.

Table 1 summarizes the measures and variables according to the timeline. Participants will be studied for 1 year following randomization. Primary and secondary outcomes will be assessed by an external nurse who will be blinded to treatment assignment after 12 months. The primary outcome will be systolic BP. Secondary outcomes will include diastolic BP, direct costs, and the number of patients who required treatment to yield one patient with normalized BP.

**Table 1 T1:** Measures, variables and timeline

VISIT	-1	0	1	2	3	4
Time (months)	-1	0	1	3	9	12
Blood pressure measurement inclusion criteria	X	X				
Morisky-Green and Haynes-Sackett tests	X					
Inclusion and exclusion criteria	X					
Comorbidities		X				
Blinded blood pressure measurement						X
Medication use						X
Adverse effects to medication		X				X
Medical consultation, cardiovascular events and hospital admission.						X
Checklist and time duration of intervention components (Intervention group)			X	X	X	
Motivational interview (Intervention group)			X	X	X	
Pill reminder (Intervention group)			X			
Family support (Intervention group)			X	X	X	
Blood pressure self-recording (Intervention group)			X	X	X	
Simplification of dosing regimens (Intervention group)			X			

Information bias will be minimized by use of a design that provides the maximum possible level of masking for studies of non-pharmacological intervention. In particular, the outcome assessor, data analyst, and physician will all be blinded to patient allocation. Misclassification, if any, is expected to be non-differential. Quality control will include recording of patient adherence to interventions, inclusion and follow-up monitoring, and quality supervision of data entry. We will perform an intention-to-treat analysis of the data; that is, the analysis will be by randomized assignment regardless of participation in intervention sessions.

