### Randomization to treatment groups

The randomization sequence will be computer-generated, stratified by nurse and blocked in groups of two. Study nurses will call the research units to give patient identification numbers and will be told the randomly assigned patient allocations. After this, participants in the intervention group will be scheduled for their first intervention visits.

The outcome assessors, data analyst, and physician will be blinded to patient allocation. To evaluate the effectiveness of blinding, these individuals will be asked to choose the arm to which they believed each patient was assigned (possible answers: intervention, usual care, or unknown). If they answered "intervention" or "usual care", they were asked to indicate what led to that belief.

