### Assessment of outcomes

#### Primary outcome measure

The primary outcome measure is systolic BP at 12 months. BP will be measured according to ESH/ESC guidelines. Patients (instructed to not eat or smoke for 30 min) will be seated quietly, with their backs supported and feet on the floor for 5 minutes. Then, using an appropriately sized cuff, the bared arm will be supported, and an oscillometric BP machine with a printer will be used for three measurements. The nurse (blinded to patient allocation) will write all three BP measurements on the final visit form.

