### Statistical Analysis

The primary statistical analysis will determine if our multifactorial intervention to improve AHT adherence is effective in lowering systolic BP and if the intervention is cost-effective. We will use intention-to-treat analysis for all data analyses; that is, all randomized patients will be included in the analysis, regardless of participation in any treatment sessions. This approach reduces the bias that may occur when participants who do not receive assigned treatments are excluded from analysis. All tests will be two-sided and α-values of 0.05 will be considered statistically significant.

We will test for significant differences between baseline characteristics of control and intervention groups. We will perform descriptive analysis, with continuous variables summarized by their means and standard deviations for normal distributions, and by median and 25^th ^and 75th percentiles for non-normal distributions.

In bivariate analysis, we will compare systolic and diastolic BP between the intervention and control groups at visit 4 (12th month) using the Student's *t*-test if both sample groups had normal distributions or the Mann-Whitney U test against the usual null hypothesis of no difference between means if the sample groups had non-normal distributions. We will also calculate 95% confidence intervals to assess the clinical significance of our treatment.

In multivariate analysis, we will adjust for clinical inertia (physicians blinding and number of medication changes) in a multiple linear regression model.

We will test for a significant difference in the percentage of patients with controlled BP (according to ESH/ESC guidelines) in the intervention and control groups using the χ^2 ^test. We will estimate relative and absolute risk reduction and the number needed to treat, defined as the estimated number of patients who need to be treated with the intervention (rather than the usual care) for one additional patient to be controlled. The 95% confidence intervals for these calculations will be provided. The number needed to treat is calculated as the reciprocal of the difference between the proportion of patients controlled in the intervention group and the control group.

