An analysis of direct costs and outcomes for patients in both groups will be conducted by a nurse blinded to patient allocation. Clinical record review and detailed self-reported data on costs of healthcare utilization, clinical tests, and medication will be considered. All resources utilized will be multiplied by the appropriate cost using nationally applicable cost data. The cost of resource utilization (primary care visits, hospital admissions, clinical testing) will be estimated using the healthcare costs published in the *National Official Journal of Spain *or *Regional Officials Journal*. Costs of all AHTs will be calculated using prices published in the catalogue of pharmaceutical compounds by the Spanish Board of Pharmacists. Intervention costs will also consider the time needed to train nurses and the time of each intervention visit.

The primary health outcome for the cost analyses is BP reduction, which will be calculated using direct costs. The measure of "relative value for money" from the intervention is the incremental cost-effectiveness ratio calculated from the additional cost for a benefit of 1 mmHg reduction.

Analysis of costs may require variable transformation, but can be modeled using multivariate linear regression without a baseline value for costs because this value will be unknown. We will adjust for age, sex, and comorbidities that may affect cost. We recognize that we will have low statistical power to detect even moderate cost differences between the two groups.

Each nurse will provide intervention to a group of patients, so we will also measure the effect of individual nurses on outcome by multilevel analysis to determine if there is a significant variation across nurses that cannot be explained by random variation, also we will establish a number maximum of 10 patients per nurse to minimize this effect.

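### Month-12 systolic BP is compared between arms without baseline systolic BP, and the planned multilevel model is not tied to the treatment estimate: a free gain in precision is left unused

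*Protocol article*

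**What the plan says.** The Primary outcome measure section fixes the endpoint: "The primary outcome measure is systolic BP at 12 months". Under Statistical Analysis, the bivariate step reads "we will compare systolic and diastolic BP between the intervention and control groups at visit 4 (12th month". It uses Student's t-test if both samples look normal, "or the Mann-Whitney U test against the usual null hypothesis of no difference between means" otherwise. No covariate is named for that comparison.

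The same section then describes one adjusted BP model: "we will adjust for clinical inertia (physicians blinding and number of medication changes) in a multiple linear regression model". The Limitations section repeats those two covariates. Neither place mentions baseline BP.

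Table 1 has a row for "Blood pressure measurement inclusion criteria", marked at months -1 and 0, so every randomised patient has pre-treatment BP on record.

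On nurses, randomisation is "stratified by nurse and blocked in groups of two". The sample-size section says clustering by nurse will be considered in the analysis. At its end, the Statistical Analysis section adds that "we will also measure the effect of individual nurses on outcome by multilevel analysis to determine if there is a significant variation across nurses", and caps the number of patients per nurse at 10.

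**The concern.** Pre-treatment systolic BP would normally be expected to predict month-12 systolic BP. It is already collected, and using it as a covariate narrows the confidence interval without bias. Leaving it out has two consequences. The standard error is larger than it needs to be, and any chance difference in baseline BP between arms passes into the estimated effect. The protocol does plan to test for baseline differences, but it gives no use for the result, so an imbalance would be reported and left in place.

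The adjusted model does not repair this. Physician blinding status and number of medication changes both arise after randomisation and may themselves depend on allocation. That model therefore cannot serve as a baseline-adjusted estimate of the total effect.

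The cost analysis shows that the authors had baseline adjustment in mind. They explain that costs will be modelled without a baseline value because none will be known. For systolic BP the baseline value is known, and no reason is given for leaving it out.

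A smaller point concerns nurses. They define the randomisation strata and deliver the intervention, so the treatment estimate should come from an analysis that includes nurse. The multilevel analysis is described as an addition, aimed at whether nurses vary. The text does not say whether it supplies the treatment effect, or which result counts if it and the t-test disagree.

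**Working it through.** **The plan's own figure.** The protocol states no standard error or confidence-interval width for the treatment effect. Its nearest figure is 110 per group, for 6 mmHg, SD 15, two-sided 0.05 and 20% loss, with no power stated. With n = 2·SD²·(z₁₋α/₂ + z_power)²/δ² per arm:

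- 80% power: 99 evaluable, and 99/0.8 = 124 randomised.
- 75% power: 87 evaluable, and 87/0.8 = 109 randomised.

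So 110 fits about 75% power, not 80%. That is a separate matter and nothing below depends on it. The calculations use the stated final size of 320.

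**Inputs from the protocol.** 320 patients allocated equally gives 160 per arm; with 20% loss, 160 × 0.8 = 128 evaluable per arm. SD 15 mmHg. Target difference 6 mmHg. Expected contamination 15%, which if taken as simple dilution leaves 6 × 0.85 = 5.1 mmHg.

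**Inputs assumed.** The correlation r between baseline and month-12 systolic BP, and the nurse intraclass correlation (ICC). The documents give neither.

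**Baseline adjustment.** The unadjusted SE is 15 × √(2/128) = 1.875 mmHg. With baseline as covariate, the residual SD is 15 × √(1 − r²). Power is from the two-sided t-test at 0.05.

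| r (assumed) | Residual SD | SE | 95% CI half-width (1.96 × SE) | Power, 6 mmHg | Power, 5.1 mmHg | Patients needed relative to unadjusted (1 − r²) |
|---|---|---|---|---|---|---|
| none | 15.0 | 1.88 | 3.7 | 89% | 77% | 1.00 |
| 0.3 | 14.3 | 1.79 | 3.5 | 92% | 81% | 0.91 |
| 0.5 | 13.0 | 1.62 | 3.2 | 96% | 88% | 0.75 |
| 0.6 | 12.0 | 1.50 | 2.9 | 98% | 92% | 0.64 |

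**Chance imbalance.** If the baseline SD is also 15 (assumed), the regression slope on baseline equals r. A one-SE imbalance of 1.875 mmHg then shifts the unadjusted estimate by r × 1.875 = 0.6 / 0.9 / 1.1 mmHg at r = 0.3 / 0.5 / 0.6, against a 6 mmHg target.

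**Nurse strata.** Stratified 1:1 allocation balances the nurse effect across arms, so the true variance of the difference is (1 − ICC) times what the t-test assumes. For ICC 0.02 to 0.10, the t-test overstates the variance by 1/(1 − ICC) − 1 = 2% to 11%, or about 1% to 5% on the SE. The direction is conservative: the true type I error is about 0.048 to 0.039. Using the strata moves power for 5.1 mmHg from 77.9% to 78.5% at ICC 0.02, and from 78.8% to 81.8% at ICC 0.10 (normal approximation).

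**Effect varying by nurse.** Suppose a nurse at the cap of 10 has 5 intervention patients, of whom 5 × 0.8 = 4 are evaluable. A within-nurse correlation of 0.05 confined to that arm (assumed) inflates its variance by 1 + (4 − 1) × 0.05 = 1.15. The variance of the difference rises by (1.15 + 1)/2 = 1.075, so the SE rises by about 3.7%. This works against the strata effect.

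**The case against.** The strongest reply is that nothing here is invalid. An unadjusted comparison of randomised arms is unbiased, and it matches a sample size built on an SD of 15 with no covariate. At 6 mmHg and 128 per arm, power is already about 89%, and a correlation of 0.3 adds only about 3 points. Enrolling only uncontrolled patients restricts the baseline range and tends to lower the correlation. The protocol itself expects regression toward the mean. All of this stands. It limits the point to precision and chance imbalance, and makes the larger gains in the table conditional. It gives no reason to leave the covariate out, since even the lowest correlation shown gives a gain.

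A reader might infer that the protocol ignores nurse clustering. The documents do not support that: they promise to consider it, plan a multilevel analysis and cap patients per nurse. What remains is the missing link between that model and the treatment estimate. A condensed article might leave the ranking of analyses to an analysis plan. Here, however, the article does state what the multilevel analysis is for, and estimating the treatment effect is not part of it.

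A reader might also treat the t-test as the declared primary test. The protocol never gives it that label; it is simply the only between-arm test named for the primary outcome. Nor does a 15% understatement of variance apply to the treatment difference. That figure concerns one arm under an assumed scenario, and becomes about 7.5% for the difference.

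**Conclusion.** The point holds as a free improvement. The only between-arm test named for month-12 systolic BP leaves out a baseline measurement that every patient has, and the one adjusted BP model cannot take its place. With SD 15, 128 evaluable per arm and an assumed correlation of 0.3 to 0.6, adjustment cuts the SE by about 5% to 20%. It adds roughly 3 to 9 points of power at 6 mmHg and 4 to 15 points at 5.1 mmHg. The correlation is not in the documents and could lie at the low end. The nurse element is minor: the multilevel model should be tied to the treatment estimate, but ignoring the strata costs little and errs on the conservative side.

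The documents do not support the stronger conclusion that the planned comparison is biased or invalid and must be corrected before the trial can be interpreted.

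**What to change.** In the Statistical Analysis section, name one primary analysis: a linear model of month-12 systolic BP on arm and baseline systolic BP, with nurse included as the stratification factor (fixed effect or random intercept) and kept whatever its significance. Report the adjusted mean difference with its 95% confidence interval. State which pre-treatment reading, or which average of the two, serves as baseline.

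- Use the same model for diastolic BP.
- Keep physician blinding and number of medication changes out of this model.
- Keep the unadjusted comparison as supportive.
- Treat a random nurse-by-arm effect as a sensitivity analysis only. With about 4 evaluable patients per nurse in each arm at most, it will be weakly estimated.
- Leave BP control on the proportion scale as planned, because the risk difference and number needed to treat do not follow directly from a mixed logistic model.

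The cost is wording, settled before unblinding. Every variable is already collected, and no patients or visits are added.

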### Statistical Issues

#### Sample size, clinical significance, statistical significance

We want to ensure that our clinical trial has adequate statistical power to detect a clinically significant difference of at least 6 mmHg at 1 year in systolic BP between groups with a two-tailed significance level of 0.05. Assuming a standard deviation of 15 mmHg and a 20% loss to follow-up, we would need to randomize 110 participants per group. We expect a 15% "contamination" of the control group (see below), yielding a 1.41 contamination effect [26]. Thus, the final target sample size is 320 patients.

The effectiveness of the intervention will be assessed by a clinically significant reduction in BP, cardiovascular mortality models shows an estimated 5-yr risk reduction of cardiovascular disease of 15-20% by a reduction of 5 mmHg in systolic blood pressure [27,28]. We have estimated that a difference of at least 10 mmHg at 1-yr is necessary to detect a clinically significant difference of at least 5 mm Hg at 5-yr.

Intervention will be provided to a group of participants by a single nurse, so we will consider the cluster effect during statistical analysis.

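### The between-arm test of 12-month systolic BP may switch to Mann-Whitney on the observed distribution, and the protocol wrongly says that test compares means

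*Protocol article*

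**What the plan says.** The Primary outcome measure section states: "The primary outcome measure is systolic BP at 12 months". The sample size section sets as its target a "clinically significant difference of at least 6 mmHg at 1 year in systolic BP between groups", tested two-sided at 5%, and adds: "Assuming a standard deviation of 15 mmHg and a 20% loss to follow-up, we would need to randomize 110 participants per group". A difference in mmHg set against a standard deviation is a difference in means.

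The Statistical Analysis section then describes a bivariate comparison of systolic and diastolic BP at the 12-month visit. It uses Student's t-test if both arms are normally distributed, and otherwise the "Mann-Whitney U test against the usual null hypothesis of no difference between means if the sample groups had non-normal distributions". The section says neither how normality is to be judged nor which quantity the promised 95% confidence intervals describe if Mann-Whitney is used.

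Two other analyses bear on systolic BP: a linear regression that adjusts for physician blinding and medication changes, and a multilevel analysis of variation between nurses. Neither depends on normality. None of the three is labelled primary, but the bivariate comparison is the only plain test of one arm against the other.

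**The concern.** There are two faults in the text. First, the null hypothesis given for Mann-Whitney is wrong. The test asks whether a value from one arm tends to exceed a value from the other. That coincides with a question about means only when the two distributions have the same shape and differ at most by a shift.

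Second, the choice of test is left to the outcome data. The quantity tested for the main outcome is therefore not fixed in advance. If the switch occurs, the p-value concerns ranks, while the effect size the trial was designed around is in mmHg. A significant rank test could then stand beside a confidence interval for the mean difference that includes zero, or the reverse, and the protocol does not say which governs.

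**Working it through.** **The plan's own figure.** The formula n = 2(z for alpha + z for power)² × SD² / difference² is a calculation for two means. With SD 15 and difference 6, 2 × 225/36 = 12.5, so n = 12.5 × (1.96 + z for power)². The protocol says only "adequate statistical power to detect" and gives no power, so 110 per group cannot be reproduced from its stated inputs alone. At 75% power, n = 87 and 87/0.8 gives 109; at 80%, n = 99 and 99/0.8 gives 124. Power is a separate matter. What counts here is that the stated inputs are those of a mean difference.

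**Patients analysed.** 320/2 = 160 per arm, and 160 × 0.8 = 128 after the 20% loss. The standard error of the difference is 15 × √(2/128) = 1.875 mmHg. A 6 mmHg effect is 6/1.875 = 3.2 standard errors, which gives 89% power. If 15% contamination dilutes the effect to 6 × 0.85 = 5.1 mmHg, power is 78%.

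**Simulation.** Assumptions, none of them from the protocol: normality judged by Shapiro-Wilk at 5% in each arm, a switch if either arm fails, and normal or shifted gamma data. SD is 15, with 128 per arm. With 6,000 replicates, the Monte Carlo standard error at a 5% rate is √(0.05 × 0.95/6000), about 0.3 percentage points.

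Equal means, percentage of trials (6,000 replicates):

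| Skewness, arm A / arm B | Switch | t-test rejects | Mann-Whitney rejects | Two-stage rule rejects |
|---|---|---|---|---|
| 0 / 0 | 10 | 5.1 | 5.2 | 5.2 |
| 0.5 / 0.5 | 76 | 5.1 | 5.1 | 5.3 |
| 1.0 / 1.0 | 100 | 5.7 | 5.6 | 5.6 |
| 0.5 / 0 | 54 | 4.9 | 6.4 | 6.3 |
| 1.0 / 0 | 99 | 5.0 | 9.6 | 9.6 |

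A separate set of 4,000 replicates covered more unequal shapes, again with equal means:

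| Skewness, arm A / arm B | t-test rejects | Mann-Whitney rejects |
|---|---|---|
| 1.0 / 0 | 5.6 | 9.7 |
| 1.0 / 0.3 | 5.3 | 7.4 |
| 1.5 / 0.3 | 4.8 | 10.5 |

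Repeat runs of these cases put Mann-Whitney at about 6-11% and the t-test at about 5%.

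**Why the rank test rejects.** At mean 140 and skewness 1.0, the gamma median is 137.5. A normal arm with mean 140 has median 140. The means agree, but the bulk of one arm lies about 2.5 mmHg below the other, and the rank test detects that.

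**Power for 6 mmHg with identical shapes.** The t-test has 89-90% power at skewness 0, 0.5 and 1.0. The two-stage rule has 89.0%, 89.8% and 93.5%.

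**Disagreement.** The two tests reach different conclusions at 5% in 2.0-5.2% of trials when shapes are identical (no effect or 6 mmHg). They differ in 4.3% and 7.7% of trials when one arm is normal and the other has skewness 0.5 or 1.0.

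**The case against.** The best defence is that little goes wrong in the likely cases. If the intervention has no effect on anyone, the two distributions are identical and Mann-Whitney keeps its error rate. If it shifts everyone equally, the rule keeps its power and at skewness 1.0 gains some. Inflation needs equal means together with different shapes. An intervention to which some patients respond strongly would normally lower the mean as well. The switch rate depends on an assumed check, and judging normality from plots could give a quite different rate. The method of checking is also the kind of detail an article may leave to a fuller document.

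All of that stands, and it limits the size of the point. It does not rescue the stated null hypothesis, which is wrong as printed, or a rule that lets the outcome data decide which quantity is tested.

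Three stronger readings may tempt a reader, and the protocol does not support them:

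- **That the switch gives up covariate adjustment.** The t-test it replaces is already unadjusted, and the regression and multilevel analyses run in either case.
- **That the cost per mmHg is affected.** That ratio is additional cost divided by mmHg reduction and does not depend on which p-value is reported for systolic BP.
- **That the protocol names this comparison as primary.** It does not. The inference is reasonable because no other plain between-arm test of systolic BP is described.

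**Conclusion.** The point holds as a wrongly described null hypothesis and an unfixed test for the main outcome. Both can be seen in the text without any simulation. After a switch, the p-value need not address the 6 mmHg mean difference and may conflict with a confidence interval for it. Whether it would conflict in this trial cannot be known, because the quantity behind the interval is not stated.

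The numerical harm is modest and conditional. Under the assumed Shapiro-Wilk rule the switch would be common with mild skewness (about 76% of trials at 0.5 in both arms). It distorts the error rate for a null of equal means only if shapes differ: about 6-11% against about 5% in the cases with skewness 1.0-1.5 in one arm and 0-0.3 in the other. A reader might infer that the trial's type I error is inflated in general. The identical-shape results (5.2-5.6% for the two-stage rule in the table) show that it is not. The switch also buys no needed protection: in every case shown, the t-test stayed within 4.8-5.7% at 128 per arm.

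**What to change.** Delete the conditional switch for systolic and diastolic BP. State that the arms are compared by the difference in mean BP at 12 months with its 95% confidence interval whatever the observed distribution, using a t-test (Welch's version if variances may differ) or an equivalent linear model. If Mann-Whitney is kept, list it as a sensitivity analysis whose null hypothesis is that neither arm tends to give higher values than the other.

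This costs a sentence or two of wording and leaves the target of 320 unchanged. Baseline adjustment and the handling of nurse effects are separate questions and are not needed for this correction.
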